### Procedure for unblinding if needed {17b}

The design is open label with only outcome assessors and data analysts being blinded, so unblinding will not occur. On the other hand, due to the nature of the intervention, the participants will know the allocation of the school.

## Data collection and management

### Plans for assessment and collection of outcomes {18a}

Data will be retrieved from:The European Drug Addiction Prevention Trial Questionnaire (EU-Dap), a self-reported questionnaire, aims to screen substance use and assess risk and protective factors among adolescents. It has 45 multi-item questions and focuses especially on tobacco, alcohol, and marijuana use. The EU-Dap instrument was developed by the research team of the Unplugged program in Europe. It was used to evaluate the Unplugged trial project, which took place between 2003 and 2005 in seven countries in Europe. In the Chilean validation study, all subscales had acceptable internal reliability (omega > 0.65) [40]. The original form of the questionnaire can be found at http://www.eudap.net.The Social Problem-Solving Inventory-Revised (SPSI-RS) consists of five scales that evaluate two dimensions of Problem Orientation (Positive Problem Orientation and Negative Problem Orientation) and three Troubleshooting styles (Rational Troubleshooting Style, Impulsive/Careless Style, and Avoidance Style). The abbreviated 25-item version [41] will be used in this study; in this shorter instrument, each scale has five items, with the full scale comprising 25 items. The inventory must be answered as a 5-choice Likert-like scale, in which the subjects indicate to what extent the proposed coping strategy applies to their characteristic way of dealing with the problems of daily life (0- it does not apply at all to me, 1- it applies slightly to me, 2- it applies moderately to me, 3- it applies a lot to me, and 4- it applies extremely to me). It has acceptable internal reliability (Cronbach alpha > 0.75) [41].The Emotion Regulation Questionnaire for Children and Adolescents (ERQ-CA). Emotional regulation is defined as the ability to control and manage one’s feelings and emotions and appears to be an important factor in social adjustment. The questionnaire consists of 10 items. The answers on the questionnaire have a five-point Likert scale quantifying the agreement to the behavior described (1 = strongly disagree, 2 = disagree, 3 = half and half, 4 = agree, 5 = strongly agree). This instrument provides scores on two uncorrelated scales: Cognitive Reappraisal (6 items) that consists of redefining a potential emotion-eliciting situation in a way that its emotional impact is changed; and Expressive Suppression (4 items), encompassing a style that consists of the inhibition of ongoing emotion expressive behavior. It has acceptable internal reliability (Cronbach alpha > 0.75) [43].The Strengths and Difficulties Questionnaire (SDQ). This is a questionnaire of 25 mental health items for a population of 4 to 17 years. It evaluates positive and negative psychological aspects, grouped into five sub-scales: (1) emotional symptoms, (2) behavioral problems, (3) attention and hyperactivity problems, (4) social relationship problems, and (5) pro-social behavior. The first four sub-scales refer to difficulties, while the last sub-scale refers to strengths. Several studies have shown that the instrument has good psychometric properties; our research team has already conducted a validation study in early adolescents in Chile [44]. This validation study confirmed the 5-dimensional structure of the instrument while also showing that its internal reliability ranges from 0.53 to 0.71 for the self-reporting version.The Psychological Sense of School Membership Scale (PSSM). The sense of school membership refers to the student’s perceptions of the respect and acceptance that teachers and other students show them and their sense of belonging. It is a scale that our research team has already validated in Chile in early adolescents. This scale has 13 items (Chilean version) and is a single dimension, with high internal reliability (Cronbach’s alpha 0.92) [45].

### Plans to promote participant retention and complete follow-up {18b}

The schools, students, and their families will receive extensive information about the study setup and requirements during the recruitment. This information will include and stress the importance of completion of follow-up. From the start of the implementation of the assessments and the lessons of “Mi Mejor Plan,” students will be reminded of the value of their active participation during the whole project. Throughout the follow-up period, the researchers will check responses and, if necessary, contact schools and participants to complete their follow-up.

### Data management {19}

After the participants have completed the questionnaires, the data will be entered into a secure platform without identifying information (each participant will be assigned an encrypted ID number). The original copies of the instruments will be filed and stored, under lock and key, in a self-storage, along with the list linking the participants’ names and ID numbers. Only the Principal Investigator, research assistants in charge of data entry, and the statistician will have access to the database. All people with access to the dataset will need to sign a Confidential Agreement to assure its commitment to not revealing identifying information.

### Confidentiality {27}

Research data will be stored using a study identification code for each participant. The key to the identification code list will only be available to the research team mentioned above and will be documented and safeguarded according to research guidelines after completion of the study. No participant identification details will be reported in publications or any study report.

### Plans for collection, laboratory evaluation, and storage of biological specimens for genetic or molecular analysis in this trial/future use {33}

Not applicable. No biological specimens will be collected in this trial.

## Statistical methods

### Statistical methods for primary and secondary outcomes {20a}

General school features (size, number of teachers, etc.) will be used to compare participating schools with those who were invited but did not participate. Additionally, descriptive statistics will compare the two arms at baseline.

Primary and secondary analysis will be conducted on an intention-to-treat basis. Odds ratios (OR) and their corresponding confidence intervals (95%CI) will be calculated as the measure of association between experimental condition (intervention arm) and behavioral outcome, controlling for baseline outcome variable scores. Secondary analysis will be conducted considering adjustment for variables with marked imbalance at baseline. Additionally, secondary analyses will be made using the secondary outcomes and analyzed with the same approach. Considering the hierarchical structure of the data and the cluster effect, a multilevel modeling approach will be followed to analyze the data. Data will be analyzed with Stata 17.0.

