### Outcomes {12}

#### Primary outcome

Cigarette use in the last month, measured with the European Drug Addiction Prevention Trial Questionnaire (EU-Dap) validated in Chile [40].

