#### Secondary outcomes

Alcohol use in the last month, measured with the European Drug Addiction Prevention Trial Questionnaire (EU-Dap) validated in Chile [40].Marijuana use in the last month, measured with the European Drug Addiction Prevention Trial Questionnaire (EU-Dap) validated in Chile [40].Social problem-solving, measured with The Social Problem-Solving Inventory-Revised (SPSI-RS) abbreviated 25-item version [41].Emotion regulation, measured with the Emotion Regulation Questionnaire for Children and Adolescents (ERQ-CA) [42, 43].Socio-emotional skills measured with the Strengths and Difficulties Questionnaire (SDQ) answered by students [44].Sense of school membership, measured with the Psychological Sense of School Membership Scale (PSSM), answered by students [45].

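### The only effect measure named is the odds ratio, and it is carried over to four secondary outcomes that are multi-item scale scores

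*Protocol article*

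**What the plan says.** In the protocol article, the section on statistical methods for primary and secondary outcomes {20a} gives a single effect measure: "Odds ratios (OR) and their corresponding confidence intervals (95%CI) will be calculated as the measure of association" between study arm and "behavioral outcome, controlling for baseline outcome variable scores". Two sentences later it turns to the secondary outcomes: "secondary analyses will be made using the secondary outcomes and analyzed with the same approach". It then adds, for the analysis as a whole, that "a multilevel modeling approach will be followed to analyze the data". No link function or distribution is named.

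The primary outcome is "Cigarette use in the last month, measured with the European Drug Addiction Prevention Trial Questionnaire (EU-Dap) validated in Chile". The list of secondary outcomes has six entries. Two are last-month use of alcohol and of marijuana. The other four are questionnaires, among them "Social problem-solving, measured with The Social Problem-Solving Inventory-Revised (SPSI-RS) abbreviated 25-item version", "Emotion regulation, measured with the Emotion Regulation Questionnaire for Children and Adolescents (ERQ-CA") and "Sense of school membership, measured with the Psychological Sense of School Membership Scale (PSSM), answered by students"; the fourth is the SDQ. The data collection section {18a} describes all four as multi-item scales and gives no cut-off for any of them.

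**The concern.** An odds ratio is a natural summary for whether a pupil used a substance in the last month. It is not a suitable measure for a sum of Likert items. For such a score it has to come from a cut-off or from an ordinal model, and the article specifies neither. This goes beyond silence on a detail, because {20a} is headed as covering the secondary outcomes and states a rule for them, and that rule does not fit four of the six.

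As written, the text leaves room for a median split, another cut-off, a proportional-odds model or a linear model. Masking the analyst to arm reduces the risk in settling this after the data are seen, but does not remove it. The scores also matter for interpretation. Eleven of the sixteen lessons teach social problem-solving, so the SPSI-RS score shows whether the programme changed what it mainly targets. The sex subgroup analyses {20b} follow the same procedures and inherit the ambiguity.

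**Working it through.** **Matching the rule to the outcomes**

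| Outcome | Form described in the article | Does an odds ratio fit? |
|---|---|---|
| Cigarette use, last month (primary) | use behaviour, sized as a difference in percentages | yes |
| Alcohol use, marijuana use, last month | use behaviour | yes |
| SPSI-RS | 25 items scored 0 to 4, five scales | not as a score |
| ERQ-CA | 10 items scored 1 to 5, two scales | not as a score |
| SDQ | 25 items, five sub-scales | not as a score |
| PSSM | 13 items, one dimension | not as a score |

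The article gives no power figure for any secondary outcome, so there is none to reproduce. Its sample size section {14} concerns cigarette use only.

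**What a split would cost, if one were made**

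Inputs from the article: 5 schools and 300 pupils per arm, hence 300/5 = 60 per school; intraclass correlation (ICC) 0.01, which {14} gives for substance use behaviours and not for these scales; significance level 0.05, taken here as two-sided. Assumptions: standardised difference d = 0.30, normally distributed scores, the cut-points, ICC 0.03 as an alternative, and no gain from baseline adjustment in either analysis.

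Power comes from a non-central t distribution with 2 × 5 − 2 = 8 degrees of freedom (critical value 2.306).

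*Continuous score, ICC 0.01*
- Design effect: 1 + (60 − 1) × 0.01 = 1.59.
- Standard error of d: √(2 × 1.59/300) = 0.103.
- Non-centrality: 0.30/0.103 = 2.91. Power: **72%**.

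*Median split, ICC 0.01*
- Proportions above the cut: 0.500 and Φ(0.30) = 0.618, a difference of 0.118.
- ICC of the split score, from a bivariate normal with correlation 0.01: (2/π) × arcsin(0.01) = 0.0064. Design effect: 1 + 59 × 0.0064 = 1.38.
- Standard error: √[(0.500 × 0.500 + 0.618 × 0.382) × 1.38/300] = 0.047.
- Non-centrality: 0.1179/0.0472 = 2.50. Power: **59%**.

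*The same steps at ICC 0.03*
- Continuous: design effect 1 + 59 × 0.03 = 2.77, standard error 0.136, non-centrality 2.21, power **49%**.
- Median split: ICC of the split score 0.0191, design effect 2.13, standard error 0.0587, non-centrality 2.01, power **42%**.

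*Other cut-points and the smaller design, ICC 0.01*

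| Design per arm | Continuous | Median split | Cut at 80th percentile | Cut at 90th percentile |
|---|---|---|---|---|
| 5 schools × 60 (8 df) | 72% | 59% | 55% | 45% |
| 4 schools × 50 (6 df) | 54% | 42% | 38% | 31% |

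The 80th and 90th percentile columns assume that the effect moves pupils into the tail above the cut. If it moves them out of that tail, the 5 × 60 figures are 47% and 35%.

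**The case against.** The strongest reply is that the odds ratio is tied to a behavioural outcome, which describes cigarette, alcohol and marijuana use. On that view, the shared approach means the other features of the paragraph: intention to treat, control for the baseline score, and a multilevel model stated without a link function. A linear mixed model for the four questionnaires would then already be compatible with the plan. The name of an effect measure for secondary scales is also something that a journal article often leaves to the analysis plan.

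This reading is possible. It does not settle the matter, because the odds ratio is the only effect measure that the sentence on secondary outcomes can refer back to, and nothing in the article points to a mean difference.

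A reader might infer something stronger: that the plan forces the scores to be dichotomised, at cut-offs chosen once the data are in. The article does not support that. It mentions no cut-off and no splitting, and a multilevel proportional-odds model yields an odds ratio for an ordered score without any cut. The power losses above would not apply to such a model. They are also smaller at an ICC of 0.03, where the median split costs about 7 percentage points against 13 at 0.01, and where both analyses have low power.

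**Conclusion.** The point holds as a mismatch between a stated rule and four of the six secondary outcomes. Taken literally, the rule leads to an unstated cut-off or an unstated ordinal model, and a better-suited analysis is readily available. The loss from a median split, 72% to 59% at ICC 0.01 and 49% to 42% at ICC 0.03, is a conditional illustration. It requires that scores are in fact split, and it rests on an assumed d of 0.30, normal scores and 5 schools of 60 per arm. No figure stated in the article changes. The primary outcome, the sample size and the two secondary use outcomes are unaffected. The text should be corrected, but the trial's main conclusion does not depend on it.

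**What to change.** Replace the sentence on secondary outcomes in {20a} with text to this effect: *Last-month cigarette, alcohol and marijuana use will be analysed by multilevel logistic regression and reported as odds ratios with 95% CI. SPSI-RS, ERQ-CA (two scales), SDQ and PSSM scores will be analysed as continuous outcomes in a linear mixed model with a school random intercept, adjusted for the baseline score, and reported as adjusted mean differences with 95% CI.* The subgroup section can stay as it is, since it refers back to these procedures.

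The cost is two sentences in the analysis section, agreed before the data are analysed. No additional data, pupils or procedures are needed.

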### Sample size {14}

For the sample size calculation, an absolute difference between the control group and the intervention group of 15% in the monthly cigarette consumption was adopted. Since students in the same educational institution show correlated behaviors, it is important to consider the nested data within the school for sample calculation. For substance use behaviors, the intraclass correlation coefficient (ICC) can be set at 0.01. Thus, with a difference between groups of 15%, statistical power of 80%, a significance level of 0.05, an ICC of 0.01, and a school size of about 50 students per school, four educational establishments, and 200 students per data collection branch are required. Considering a loss of 20% of the schools in the follow-up, we have included one more school in each arm, ending up of five schools and 300 students per arm.

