### Sequence generation {16a}

Randomization will be performed once all schools are recruited. Using computer-generated randomization, schools will be randomly assigned to either group with a 1:1 allocation.

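### The primary odds ratio rests on a multilevel model of ten schools (eight after the planned loss) with no few-cluster provision; normal-based inference would give a false-positive rate of about 7-9% at the protocol's ICC

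*Protocol article*

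**What the plan says.** The Sample size section {14} asks for four schools and 200 students per arm, then adds a school per arm against a 20% loss of schools: "we have included one more school in each arm, ending up of five schools and 300 students per arm". That makes ten schools in all, or eight if the allowance is used up. The only intraclass correlation in the document is in the same section: "the intraclass correlation coefficient (ICC) can be set at 0.01". Its scale is not given.

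The section Statistical methods for primary and secondary outcomes {20a} plans odds ratios with 95% confidence intervals, adjusted for the baseline value of the outcome, in Stata 17.0. On clustering it says "Considering the hierarchical structure of the data and the cluster effect, a multilevel modeling approach will be followed to analyze the data". The secondary outcomes follow the same approach. No estimator, test, reference distribution or degrees of freedom is named, and no small-sample correction is either named or ruled out.

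**The concern.** School is the unit of randomisation, so the information on between-school variance comes from eight to ten units. Ordinary large-sample inference from a random-intercept logistic model treats that variance as if it were well estimated and refers the Wald statistic to the normal distribution. With four or five schools per arm, neither step is safe. The variance is often estimated at or near zero, in which case the standard error is that of an unclustered analysis. When it is not zero, maximum likelihood tends to underestimate it, and the reference should be nearer to t on 6 or 8 degrees of freedom.

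Both effects make the confidence interval for the sole primary outcome too narrow and raise the chance of declaring an ineffective programme effective. The protocol picks the method and the number of schools in separate sections and does not connect them.

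**Working it through.** **Inputs.** From Sample size {14}: "statistical power of 80%, a significance level of 0.05, an ICC of 0.01"; "an absolute difference between the control group and the intervention group of 15% in the monthly cigarette consumption was adopted"; "a school size of about 50 students per school, four educational establishments, and 200 students per data collection branch are required"; then five schools and 300 students per arm. Not stated: the control-arm smoking rate, the sidedness of the test (two-sided assumed) and the scale of the ICC. Prevalence was therefore varied from 5% to 30%, and the ICC was read on both scales.

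**The plan's own figure.** The design effect is 1 + (50 - 1) × 0.01 = 1.49.
- 30% versus 15% needs 121 per arm for two proportions. 121 × 1.49 = 180, and 180/50 = 3.6, so 4 schools.
- 20% versus 5% gives 76 × 1.49 = 113, or 3 schools. 50% versus 35% gives 253, or 6 schools.
- Four schools follow for control rates from just above 25% to about 33%. The figure is thus compatible with the usual formula, which uses an ICC on the proportion scale, but it cannot be uniquely reproduced.
- School loss: 4/(1 - 0.2) = 5 per arm. Since 5 × 50 = 250, the stated 300 implies 60 per school.

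**Closed-form reference points**, K = number of schools.
- Unbiased variance, normal reference: P(|t on K-2 df| > 1.96) = 8.6% for K = 10 and 9.8% for K = 8.
- Maximum likelihood when between-school variance dominates: P(|t on K-2 df| > 1.96 × √((K-2)/K)) = 11.8% for K = 10 and 14.1% for K = 8.

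At an ICC of 0.01 that variance does not dominate. Its share of the variance of a school mean is 0.01/(0.01 + 0.99/60) = 38% with 60 students.

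**Simulation under no effect.** Random-intercept logistic model, maximum likelihood with 25-point quadrature, about 3,000 data sets per cell (Monte Carlo standard error about 0.4-0.6 points). Ten schools means 5 × 60 per arm; eight means 4 × 50. Ranges are over prevalence 5-30%.

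| ICC | Wald z, 10 schools | Wald z, 8 schools |
|---|---|---|
| 0.01, proportion scale | 7.1-9.2% | 6.6-8.5% |
| 0.01, latent scale | 4.3-6.5% | 4.1-7.0% |
| 0.02, latent scale | 4.9-8.9% | 4.2-9.1% |
| 0.05, latent scale | 6.7-11.7% | 6.0-12.4% |

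The two scales differ materially: at 20% prevalence, a latent ICC of 0.01 equals about 0.005 on the proportion scale.

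At 0.01 on the proportion scale, the school variance was estimated at practically zero in 38-40% of data sets with ten schools and in 51-53% with eight.

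**Sensitivity to a larger ICC, proportion scale.** Wald z gave about 9-12% at 0.03 and 12-13% at 0.05. Other runs of 1,200 to 2,000 data sets per cell scattered between 9.9% and 14.8% over these two values, with a standard error of up to about 1 point.

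**Alternatives, main simulation.**
- School-level t-test on K-2 df: 4.0-5.8% in every cell.
- Likelihood-ratio test: 4.4-7.7% at ICC 0.01 on either scale, at most 9.9% anywhere.
- Wald statistic referred to t on K-2 df: 1.9-5.0% (ten schools) and 0.9-3.1% (eight) at ICC 0.01.

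**Cost in interval width.** The critical value is 2.31 on 8 df or 2.45 on 6 df. 2.31/1.96 = 1.18 and 2.45/1.96 = 1.25.

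**The case against.** The best reply is that the article never says Wald z. It is a condensed account, a statistical analysis plan may exist, and the test and its degrees of freedom are details often left to it. That stands, and it is why the error rates here are conditional on uncorrected normal-based inference. It does not remove the point: the article names the primary method and the number of schools, and ordinary inference from that method does not suit that number.

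Three further replies also stand in part. At an ICC of 0.01 on the latent scale, the rate is near nominal, and at low prevalence slightly below it. A likelihood-ratio test does better than Wald z. The planned baseline adjustment could change the residual between-school variance, and the simulations did not include it.

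A reader might go further and infer an error rate of 14%, or two to three times nominal. The documents do not support this. Their only ICC is 0.01, where 7-9% is 1.4 to 1.8 times nominal and 4-7% is 0.8 to 1.4 times. The 14.1% limit needs eight schools and dominant between-school variance.

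A reader might also add the allocation ("Using computer-generated randomization, schools will be randomly assigned to either group with a 1:1 allocation") and the adjustment rule ("Secondary analysis will be conducted considering adjustment for variables with marked imbalance at baseline") as sources of inflation. They are not. Simple 1:1 randomisation is valid and chance imbalance does not raise the type I error; constraining the allocation is a design preference. The imbalance-driven adjustment is confined to a secondary analysis and cannot alter the primary p-value.

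**Conclusion.** The point holds in conditional form. With ten or eight schools, maximum likelihood, Wald z tests and no small-sample correction, the nominal 5% test has a false-positive rate of about 7-9% at the protocol's ICC on the proportion scale, and about 4-7% on the latent scale. The proportion scale is the more natural reading, because the planned size fits the usual design-effect formula, but the article does not confirm it. Rates of about 9-13% require an ICC of 0.03-0.05, which is a sensitivity range only.

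The results assume equal school sizes, prevalence of 5-30%, no baseline covariate and no imputation. The inflation is moderate, but it falls on the one primary test and can be avoided with a sentence.

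**What to change.** State in section {20a} that the primary p-value and confidence interval come from a method valid for few clusters, and name it. Two options:
- A two-stage school-level analysis: adjust for the baseline outcome, then compare school summaries by arm with t on about (schools - 2) degrees of freedom.
- A permutation test over the possible allocations. Significance stays attainable: the smallest two-sided p-value is 2/252 = 0.008 with ten schools (five per arm) and 2/70 = 0.029 with eight (four per arm).

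For continuous secondary outcomes, use REML with Kenward-Roger degrees of freedom. Keep the multilevel odds ratio as supportive. If the school-level analysis is on the scale of proportions, say which estimate is primary, and say how the method is combined with multiple imputation.

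The cost is a change of wording and wider intervals, by up to about 18% with ten schools and 25% with eight. Simply referring the Wald statistic to t on K-2 df is the easiest change but somewhat conservative at an ICC of 0.01, so a school-level or permutation analysis is preferable. No new data are needed.
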